### Management of Confounding and Interaction Factors

The use of glucocorticoids for an indication other than treatment of an irAE will be considered a confounding factor. To control for this source of confounding, the dose and duration of glucocorticoid therapy will be minimised, and multivariate analysis will be adjusted for concomitant glucocorticoid use.

The coexistence of an autoimmune disease with cancer will be considered a potential effect modifier (i.e., interaction). Furthermore, female sex is known to be a risk factor for ANA positivity and high ANA titers (Li et al., 2011). To facilitate the interpretation of these two potential interactions, data will be presented for patient subgroups in the form of contingency tables.

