## Methods and Analysis

### Objectives

#### Primary Objectives

• To identify predictive factors of irAEs at week 48 after the initiation of ICI therapy• To evaluate the diagnostic properties (sensitivity, specificity, positive predictive value, negative predictive value, likelihood ratios) of a predictive model of irAEs.

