### Study Design and Ethical Considerations

The protocol of the AUTENTIC study was designed in accordance with the Strengthening the Reporting of Observational Studies in Epidemiology guidelines. Accordingly, a multicenter observational prospective cohort study was designed with the participation of the following hospitals of the north of Spain: Araba University Hospital (Vitoria-Gasteiz), Navarra University Hospital (Pamplona), Galdakao University Hospital (Galdácano), Donostia University Hospital (San Sebastián) and San Pedro University Hospital (Logroño).

This study will be conducted in accordance with the Good Clinical Practice guidelines of the International Council for Harmonization (ICH) E6, the principles of the Declaration of Helsinki, and local regulations. Informed consent will be obtained from all participants before their enrollment. The study protocol has been reviewed and approved by the Ethical Committee of the Basque Country [code: PI2018106 (EPA-SP)] and the Spanish Agency of Medicines and Medical Devices (code: ILB-NIV-2018–01). The study has been registered in ClinicalTrials.gov (NCT03868046).

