Survival will be assessed using a Kaplan-Meier analysis and compared between groups using the log-rank Mantel-Cox test. A subgroup analysis according to tumour type and extent of cancer (local, advanced, and metastatic disease) will be performed to assess survival outcomes*.* A multivariate analysis using logistic regression and Cox regression will be performed to detect factors associated with the occurrence of irAEs. Applying a manual backward stepwise procedure, a multivariate model will be constructed from variables that either have a p-value of less than 0.10 in the univariate analysis or are considered relevant to the dependent variable on the basis of previous studies (e.g., sex and age of patients, type of ICI). Variables not reaching statistical significance will be dropped from the final predictive model. The sensitivity, specificity, positive predictive value, negative predictive value, and probability ratios with their corresponding 95% confidence intervals of the model will be calculated. The diagnostic accuracy of the predictive model inferred from the logistic regression model will be described with the area under the receiver operating characteristic curve.

Two-sided hypothesis tests will be performed, and the significance level will be set at 5%. The statistical analysis will be conducted using IBM SPSS Statistics software version 27.0 (Chicago, IL).

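### The promised adjustment for concomitant glucocorticoids is not protected from the rule that drops every non-significant variable

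*Protocol article*

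**What the plan says.** Two sections of the protocol article bear on this.

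- *Management of Confounding and Interaction Factors*: "The use of glucocorticoids for an indication other than treatment of an irAE will be considered a confounding factor". As analysis-stage control, "multivariate analysis will be adjusted for concomitant glucocorticoid use". No condition is attached.
- *Sample Size Calculation and Statistical Analysis*: "A multivariate analysis using logistic regression and Cox regression will be performed to detect factors associated with the occurrence of irAEs". Variables become candidates through a univariate p-value below 0.10, or because they are "considered relevant to the dependent variable on the basis of previous studies (e.g., sex and age of patients, type of ICI"). A manual backward stepwise procedure follows, and "Variables not reaching statistical significance will be dropped from the final predictive model". Tests are two-sided at 5%.

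The second section mentions neither glucocorticoids nor any variable that stays in regardless of its p-value.

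The first primary objective is "To identify predictive factors of irAEs at week 48 after the initiation of ICI therapy"; the second is to evaluate the diagnostic properties of a predictive model.

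**The concern.** One section says a named confounder will be adjusted for. The other says what happens to any variable whose p-value is too large. Being relevant on prior grounds gets a variable into the starting model, but nothing shields it from later removal. When the glucocorticoid term is not significant, the analyst has two instructions that cannot both be met in the final model, and the choice would be made with the p-value in view.

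Significance is also a poor criterion for keeping a confounder. The p-value depends on how many patients use glucocorticoids and how many irAEs occur. Confounding depends on how the variable relates to both the panel and the irAE. A term can miss p < 0.05 and still move the panel estimate.

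At stake is the reported association between the autoantibody panel and irAEs. If glucocorticoids lower both panel positivity and irAE risk, dropping the term overstates the association. If users are more often panel-positive, the error runs the other way.

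**Working it through.** **1. The two rules side by side**

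| Glucocorticoid term | Confounding section | Statistical section |
|---|---|---|
| p < 0.05 | adjust | keep |
| p ≥ 0.05 | adjust | drop |

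The rules collide in the second row, so the next question is how often that row would occur.

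**2. Inputs from the article**

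- Planned size: 70/0.25 = 280 patients (70 with and 210 without an irAE), and 280 × 1.05 = 294, the stated total.
- Panel positivity, from the pilot study in the Discussion (87.5% with and 30% without an irAE): 0.25 × 0.875 + 0.75 × 0.30 = 0.444.
- Panel odds ratio given glucocorticoid use: 3.25, from one retrospective lung cancer study in Table 1.

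**3. Assumptions**

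The article gives no figure for glucocorticoid use or effect. Main scenario: use in 10%, 20% or 30% of patients, with odds ratio 0.5 for irAE and 0.5 for panel positivity.

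**4. Chance of losing the term: analytic check at 20% use**

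With an irAE odds ratio of 0.5 and 25% irAEs overall, the risks are 0.158 in 56 users and 0.273 in 224 non-users. The expected cells are 8.85, 47.15, 61.15 and 162.85.

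SE(log OR) = √(1/8.85 + 1/47.15 + 1/61.15 + 1/162.85) = 0.396

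|ln 0.5| / 0.396 = 1.75

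Chance of p < 0.05 ≈ Φ(1.75 − 1.96) ≈ 0.42, so the term is dropped about 58% of the time. Simulation of 4,000 studies with the panel in the model gives 58.5%.

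**5. Size of the shift: 20% use, exact collapse**

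Panel positivity is 0.313 in users and 0.477 in non-users. The irAE risks are:

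- non-users: 0.397 (panel-positive) and 0.168 (panel-negative);
- users: 0.248 (panel-positive) and 0.092 (panel-negative).

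Averaging over users and non-users:

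- panel-positive: (0.3814 × 0.397 + 0.0626 × 0.248)/0.444 = 0.376;
- panel-negative: (0.4186 × 0.168 + 0.1374 × 0.092)/0.556 = 0.1495.

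Odds ratio without the term = (0.376/0.624)/(0.1495/0.8505) ≈ 3.43, against 3.25.

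**6. Main scenario**

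| Use | Term dropped | Panel OR without it | Shift from 3.25 |
|---|---|---|---|
| 10% | 75% | 3.34 | +3% |
| 20% | 59% | 3.43 | +5% |
| 30% | 46% | 3.49 | +7% |

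Adding the univariate p < 0.10 entry rule changes the drop probability by less than 0.5 percentage points.

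**7. Wider range**

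With odds ratios of 0.3 to 0.7 for irAE and 0.3 or 0.5 for panel positivity, the drop probability runs from about 8% to 90%, and the shift from about +2% to +21.5%. The largest shift (3.95 against 3.25) goes with the lowest drop probability (8.5%).

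**8. Against sampling error**

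With 280 patients, SE(log panel OR) is about 0.29. The 95% interval around 3.25 is exp(ln 3.25 ± 1.96 × 0.29), or 1.8 to 5.7. The largest main-scenario shift is ln(3.493/3.25) = 0.072, a quarter of one standard error.

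**The case against.** The strongest reply is that the two sentences concern different things. The promise covers the multivariable analysis; the drop rule covers the final predictive model. An adjusted association model alongside a reduced predictive model would satisfy both. That reading is possible, but the article describes only one model-building process, states its aim as detecting associated factors, and mentions no separate adjusted model. If two models are meant, a sentence should say so.

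It can also be said that a specific commitment overrides a general rule, that the list of relevant variables is only illustrative, and that forced-in covariates are usually left to an analysis plan. The list is indeed illustrative, and leaving glucocorticoids out of it proves nothing. But the point does not rest on an omission: both rules are written, and nothing says which prevails.

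Several objections about weight do stand:

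- Patients on prednisone above 10 mg/day or equivalent are excluded at entry (*Participants*). This limits baseline exposure to low doses and makes the larger assumed effects unlikely.
- The inputs are mixed. The pilot rates imply a panel odds ratio of (0.875/0.125)/(0.30/0.70) ≈ 16, while 3.25 comes from a different panel in lung cancer only.
- Weighting each main-scenario shift by its drop probability gives roughly 0.75 × 3%, 0.59 × 5% and 0.46 × 7%, or 2% to 3%.

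A reader might infer that the reported sensitivity, specificity and area under the curve are biased too. The documents do not support that: these describe the model actually built, and a prediction model need not contain every confounder.

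A reader might also take "To control for this source of confounding, the dose and duration of glucocorticoid therapy will be minimised" as study-driven care that undercuts the statement that "a multicenter observational prospective cohort study was designed". The documents do not support this either: *Follow-Up Methods* says patients are monitored according to standard recommendations, and nothing shows that care would differ from usual practice.

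**Conclusion.** The inconsistency is real and worth correcting before analysis. As written, a p-value can remove an adjustment that the article promises, and for a moderate confounder with 70 planned cases that outcome is likely: about 46% to 75% in the main scenario.

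The numerical consequence is small. When the term is dropped, the panel odds ratio moves by about +3% to +7%, well inside sampling error. These figures rest on assumed glucocorticoid use and effects and on a model with only the panel and glucocorticoids. The sign follows from assuming that users are less often panel-positive, so the true direction is unknown. Without a link to panel positivity there is no confounding shift; only the slight non-collapsibility of the odds ratio would remain.

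The point bears on the first primary objective through the reported panel–irAE association. It does not show serious bias in the study's main result.

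**What to change.** Add to *Sample Size Calculation and Statistical Analysis*: concomitant glucocorticoid use for non-irAE indications is kept in the multivariable logistic and Cox models of the panel–irAE association whatever its p-value. Limit significance-based reduction to the other variables. Report any reduced predictive model, with its sensitivity, specificity and area under the curve, separately from the adjusted association.

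The cost is a short addition to the text and one extra model parameter with 70 planned cases. Sample size and significance level do not change, and no data are needed beyond those that the promised adjustment already requires. The change should be made before the association results are seen.

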### Summary

We are currently witnessing an exponential increase in publications on irAEs; most of them focus, however, on identifying predictors of efficacy rather than toxicity (Hopkins et al., 2017). Nevertheless, recent years have seen the emergence of several methods seeking to achieve early detection of irAEs (Patil et al., 2018; Nakamura, 2019; von Itzstein et al., 2020), namely, analysis of lymphocyte subpopulations (Das et al., 2018), autoantigen microarrays (Gowen et al., 2018; Tahir et al., 2019), molecular omics data (Jing et al., 2020), gene signatures and polymorphisms (Friedlander et al., 2018; Abdel-Wahab et al., 2021), and the gut microbiome (Dubin et al., 2016). All these still experimental tools share the drawback of a high level of complexity, limited availability, and high cost. In parallel, other more accessible risk factors and markers have been suggested, namely, female sex (Valpione et al., 2018), total white blood cell and lymphocyte counts (Fujisawa et al., 2017), peripheral eosinophilia (Chu et al., 2020), sarcopenia (Daly et al., 2017), vitamin D deficiency (Bersanelli et al., 2017) and levels of more easily measurable interleukins (ILs) such as IL-6, IL-17 and IL-10 (Sun et al., 2008; Tarhini et al., 2015). Overall, there is a need for better clinical and immunological characterization of patients who develop irAEs, especially those with pre-existing ADs. Despite systematization efforts (Haanen et al., 2018; Schneider et al., 2021), it remains unclear how best to manage irAEs, and to tackle this question, there is a need to thoroughly understand the duality between the anti-tumor and the immunogenic effects of ICIs.

For all these reasons, the AUTENTIC study aims to investigate the usefulness of a sensitive, accessible, and inexpensive panel of autoantibodies, consisting of ANAs, RF, and ANCAs, to detect patients at risk of developing irAEs induced by ICIs. We also aim to describe the autoantibody profile, the potential early appearance or aggregation of autoantibodies over time, and the impact of irAEs on cancer-related survival of patients receiving ICIs.

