Within the AUTENTIC project, we have recently published a retrospective, single-center, pilot study showing a potential association between autoantibody positivity, considering an autoantibody battery consisting of ANAs, RF, ANCAs and anti-thyroid antibodies, and the occurrence of irAEs in 69 patients treated with nivolumab (Les et al., 2021). A hallmark of that study is that we included patients diagnosed with various types of cancer, non-small cell lung cancer being the most common. Overall, 37.5% of the cohort experienced at least one irAE. We observed that the autoantibody panel positivity was significantly higher in patients experiencing irAEs (87.5 vs. 30% in those not experiencing irAEs, *p* = 0.009). Consistent with previous evidence, other factors that could influence the appearance of irAEs were young age and female sex. The statistical model based on sex, age at ICI initiation and positivity for any autoantibody included in the battery predicted the occurrence of irAEs with an area under the receiver operating characteristic curve of 90.6%. In the logistic regression model, the only independent predictive factor of irAEs was positivity in the autoantibody panel under study (OR = 46.61, *p* = 0.010). Furthermore, a marked overlap was demonstrated between the different autoantibodies under study.

Besides these studies assessing some routinely available autoantibody panels, other approaches that apply throughput autoantigen array technology should be considered. For example, using serological analysis of recombinant cDNA expression, a technique designed to detect tumor antigens, Tahir et al. found anti-GNAL and anti-ITM2B autoantibodies correlated with hypophysitis and anti-CD74 antibodies correlated with pneumonitis (Tahir et al., 2019). Further, applying a human proteome microarray system called HuProt, Gowen et al. identified a specific pre-treatment autoantibody profile in the serum of patients, which was associated with severe irAEs (Gowen et al., 2018).

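### Sex is labelled only a potential interaction and can be dropped by backward selection, so the panel's odds ratio may be reported without sex adjustment; the expected bias is modest.

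*Protocol article*

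**What the plan says.** **Management of Confounding and Interaction Factors.** One confounder is named, glucocorticoid use for reasons other than an irAE, with the promise that "multivariate analysis will be adjusted for concomitant glucocorticoid use". Coexisting autoimmune disease is called a potential effect modifier. The section then states that "female sex is known to be a risk factor for ANA positivity and high ANA titers", counts sex as the second of two potential interactions, and adds that "data will be presented for patient subgroups in the form of contingency tables". It does not mention adjustment for sex.

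**Summary (Introduction) and Discussion.** The Summary says that "other more accessible risk factors and markers have been suggested, namely, female sex", among others. The Discussion, describing the pilot study, says that "other factors that could influence the appearance of irAEs were young age and female sex". It also reports that in the pilot's logistic model "the only independent predictive factor of irAEs was positivity in the autoantibody panel under study".

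**Sample Size Calculation and Statistical Analysis.** Candidates for the multivariable model are those with a univariate p-value below 0.10 or with support from earlier research. Sex, age and ICI type are the examples of the second kind. Selection is backward, and "Variables not reaching statistical significance will be dropped from the final predictive model". Tests are two-sided at 5%. No variable is exempt from removal.

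**The concern.** The reason given for treating sex as an interaction is that it is associated with the test. That is no evidence that the panel's effect differs between women and men. With the suggested link to irAEs, the article's own statements describe the pattern of a potential confounder.

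The label matters because of the removal rule. A covariate held for confounding control is kept whatever its p-value, while a candidate predictor is not. If sex fails the 5% test, the final model reports the panel's odds ratio without sex adjustment, and part of any sex effect on irAEs is credited to the panel. The first primary objective is to identify predictive factors, and the pilot presented the panel as the only independent one. The main study's result is likely to be read the same way.

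**Working it through.** **1. The plan's own size.** 70 irAE cases at a 25% rate give 70 / 0.25 = 280 patients, of whom 210 have no irAE. 280 × 1.05 = 294, the stated total. The evaluable size used below is 280. Nothing in this point disputes that figure.

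**2. Assumed inputs.** The documents give no size for either sex link. Assumed: 35% women; panel positive in 45-50% of women and 20-25% of men; sex-irAE odds ratio (OR) 1.5 to 2.0. The 25% irAE rate is the plan's.

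**3. Upper bound: sex never in the model, no true panel effect.** Strongest case: 50% of women and 20% of men positive, sex OR 2.0.
- The irAE risks solving 0.65 × p(men) + 0.35 × p(women) = 0.25 with OR 2.0 are 0.203 and 0.337.
- Panel-positive: 0.35 × 0.50 = 0.175 women and 0.65 × 0.20 = 0.130 men. Risk = (0.175 × 0.337 + 0.130 × 0.203) / 0.305 = 0.280.
- Panel-negative: 0.175 women and 0.520 men. Risk = (0.175 × 0.337 + 0.520 × 0.203) / 0.695 = 0.237.
- Crude OR = (0.280 / 0.720) / (0.237 / 0.763) = 1.25.

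Mildest case: 45% and 25% positive, sex OR 1.5.
- Risks are 0.223 in men and 0.301 in women.
- Panel-positive: (0.1575 × 0.301 + 0.1625 × 0.223) / 0.320 = 0.261.
- Panel-negative: (0.1925 × 0.301 + 0.4875 × 0.223) / 0.680 = 0.245.
- Crude OR = 1.09.

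So 1.09-1.25 is the bias if sex were always left out.

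**4. Bias under the stated rule.** In simulated cohorts of 280, irAE was regressed on panel and sex, and sex was removed if p ≥ 0.05.

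| Quantity | Result |
|---|---|
| Cohorts in which sex is dropped | about 34-75% |
| Inflation of panel OR when sex is dropped | about 5-14% |
| Inflation averaged over all cohorts | about 3-6% |

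Repeating this with a true panel OR of 1 and of 3.25 moved these limits by no more than about two percentage points.

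A second assumed set gives a similar picture: 40% panel-positive overall, sex-panel OR 1.5-3, sex-irAE OR 1.5-2.5, true panel OR 1-3.25. Sex is dropped in about 12-72% of cohorts, with mean inflation of 2-12% when dropped and about 1-5% overall. With no panel effect, the panel is declared significant in 5-7% of cohorts under the rule, against 4.5-6% with sex kept.

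**5. Why step 4 is smaller than step 3.** On the log scale, the bias is roughly the estimated sex coefficient times the difference in the share of women between panel groups. In the strongest case that is ln 2.0 × (0.175/0.305 − 0.175/0.695) = 0.693 × 0.322 = 0.223, or a factor of 1.25, as in step 3. The rule removes sex when its estimated coefficient is small, and so when its confounding is small. The overall figure is then diluted by the cohorts that keep sex. For one scenario of the second set (sex-panel OR 2, sex-irAE OR 1.5, no panel effect): share dropped 0.715 × ln 1.042 = 0.029, a factor of 1.03.

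**The case against.** - **Sex is not handled by tables alone.** The statistical section enters it as a candidate whatever its univariate p-value. This stands, and the point is therefore conditional on removal. On the Discussion's account the pilot model found only the panel to be independent, so removal is a realistic outcome.
- **Tables split by sex do hold sex constant.** A reader might infer that they give no control for sex at all. That is not supported: a panel-by-irAE table within one sex is free of confounding by sex. What they lack is a single adjusted estimate.
- **The link to irAEs is tentative.** A reader might call sex a known common cause. The article says only that it has been suggested and could have an influence, so *potential confounder* is the right term.
- **Prediction does not need confounder control.** This stands for the second primary objective. Sensitivity, specificity, predictive values and ROC area describe the model as built. It does not cover the reading of the panel as an independent factor.
- **The bias is small beside the pilot's contrast.** Panel positivity of 87.5% against 30% gives a crude OR of (0.875/0.125) / (0.30/0.70) = 16.3. An inflation of 5-14% would not alter a finding of that order, though it weighs more if the main study finds a weaker association.
- **Effect modification.** A reader might infer that claims of interaction will rest on comparing tables by eye. The article calls the tables an aid to interpretation. It does not say they are the only analysis, and it states no rule for claiming an interaction. Model terms may stand in the full protocol or analysis plan. This part is only an optional addition.

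**Conclusion.** The point holds in a limited form. On the article's own statements sex is a potential confounder of the panel-irAE association, the section on confounding treats it only as an interaction, and the removal rule can leave the panel's odds ratio without sex adjustment.

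The harm is modest: about 5-14% inflation when sex is dropped and about 3-6% on average, under the assumed values. Every sex-related input is an assumption, and the simulated model holds only panel and sex, so a fuller selection could behave differently. It would be wrong to take 1.09-1.25 as the expected bias, or to combine it with the drop rate, because that range applies only if sex is always omitted. The documents give no ground for saying that the diagnostic-accuracy results are biased by this. The case for acting rests on the low cost of the remedy rather than on a large expected error.

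**What to change.** 1. In Management of Confounding and Interaction Factors, name sex as a potential confounder of the panel-irAE association.
2. In Sample Size Calculation and Statistical Analysis, exempt sex from removal in every multivariable model, logistic or Cox, that reports the panel's effect.
3. Report the panel's crude and sex-adjusted odds ratios together, with 95% intervals.
4. Optionally, alongside the planned tables, give panel-by-sex and panel-by-autoimmune-disease interaction estimates with 95% intervals, labelled exploratory. These intervals will be wide, especially for autoimmune disease.

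**Cost.** One retained covariate that is already collected, slightly wider intervals for the panel's effect, and up to two exploratory models. The sample size does not change.
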